### Intervention control group

Participants will follow the usual intervention, according to the protocols in each centre, as it is described elsewhere [8]. The visits will be done every 3 months, including advice on life-style changes, physical exercise, hypo caloric diet, containing 1,200-1,500 kcal and anthrometric measurements (weight, height and waist perimeter). Follow up of blood tests by a healthcare professional will be done at the beginning, at one year and at the end of the study. In additional file 1 it is described the content of their visits.

### Motivational intervention in the intervention group

Participants will follow the usual intervention, the same as in the control group, plus a group motivational intervention every 15 days, at the initial weeks 1 and 12 of the intervention, following the LEARN (Lifestyle, Exercise, Attitudes, relationships and Nutrition) programme [12] and then monthly at weeks 13 and 32, following the instructions of the Weight Maintenance Survival Guide programme [13]. Each session would last for one hour, for a 26 month follow up period, with a total of 32 interventions, as described in Table 4. Request for blood test at the start, at one year and at the end (3-year study duration). In additional file 2 it is described contents of the visit.

**Table 4 T4:** 32 group sessions of the intervention.

In **sessions 1 to 4** (fortnightly) we should raise awareness among the patients of the benefits of changing their habits, which will allow us to move from the **"pre-contemplation" **to the **"contemplation" **stage.
To do this we must provide them with ample information about the benefits of change, the recommended diets which will be dealt with individually with the nurse or doctor, physical exercise, etc.
This will be reinforced with the instructions given to individuals.
1. We will explore their fears, earlier failures, worries and difficulties that prevent them from taking the decision.
2. We will help sort out their doubts about unhealthy behaviour or habits to encourage life style changes towards a healthier life.
3. We will give them the tools they need to face situations where their usual strategies have failed.
4. We will encourage the patient to move towards the desire to change, attempting to help them recognise and take care of their present and future problems and strengthening their perception of the effects.
5. We will work on the patients' resistance.

In **sessions 5 to 12** (fortnightly) we will have dispelled the patients' doubts and they will feel motivated to make a change to healthy habits and be committed to continuing with the programme.
We will then move into the "**determination" **stage
**1. **Reinforce the patient's self-motivational affirmations.
**2. **Point out the positive and negative aspects of the behaviour to suppress, the old and the new to be acquired.
**3. **Elaborate on these by asking for examples, clarifying the how, when, why...
**4. **Use extremes and image the best and worst results of the changes as well as their possible consequences.
**5. **Look backwards and/or forwards. Visualise with the patient what it was like before and how he/she thinks, he/she is going to feel once he/she has given up this unhealthy habit.
**6. **Explore the feelings associated with the change (fear, anxiety, etc)
**7. **Explore if he has help and support from a partner/family.
**8. **Strengthen the active role the patient has in the change.
**9. **Understand the resistance to change.
**10. **Help develop strategies.
**11. **Develop a joint action plan
**12. **Combat feelings of loss caused by the change.

In **sessions 13 to 32** (monthly) work with **"changes" **and **"maintenance"**.
**1. **Bolster the capacity to change
**2. **Encourage the patients to give their own reasons.
**3. **Increase the consciousness towards change.
**4. **Understand the stress these changes in habits cause in the patients
**5. **Reinforce the benefits of change.
**6. **Bolster self-efficacy.
**7. **Support the changes.
**8. **Boost each member's capacity to make a change.
**9. **Understand the patients' emotions and thoughts.
**10. **Give empathetic responses.
**11. **Assist with the expression of feelings and emotions.
**12. **Prevent relapses through exploration
**13. **Identify risky situations and find strategies for dealing with them.
**14. **Support the work and efforts made and the benefits of change and maintenance of their decision.

From 1 to 12, fortnightly sessions, from 13 to 32, monthly sessions.

### Objectives of the psychological support

Table 5 describes the main objectives proposed for the interventional group, aimed to facilitate the awareness and compliance with a series of requirements for lifestyle changes that will reinforce the medical follow up by creating intervention groups with psychological support to be conducted by nursing staff (previously trained by expert psychologists), [26,27]:

**Table 5 T5:** Objectives of the physcological support:

•Give patients the opportunity to explain their difficulties, to achieve the required objectives.
•Share their experiences and feelings with one another from their group team.
•Enable the appearance and elaboration on the anxiety that arises with lifestyle changes.
•Reinforce the changes made.
•Explain the benefits of these new attitudes.
•Clear up any doubts.
•Induce shared positive reinforcement.

The Stages through which the patient passes before taking the decision to change his or her habits, following the Prochaska model [29], are described in Table 6.

**Table 6 T6:** Stages in the intervention group:

A) Pre- contemplation	1. Give the patient plenty of advice 2. Guide the patient in relation to the programme 3. Get commitment through the motivational interview. 4. Evaluate the willingness and motivation to make changes.
B) Contemplation	1. Evaluate willingness and motivation to make the changes 2. Get a realistic commitment through the motivational interview 3. Reach an agreed decision to change behaviour and habits.

C) Preparation for action	1. Create an action plan within the group, adapting this to individual possibilities 2. Invite the family to collaborate.

D) Action	1. Introduce initiation of prevention of relapses during the group sessions. 2. Introduce advice, educational activities about healthy eating habits and smoking. 3. Include reinforcement for achievements.

E) Maintenance	1. Introduce maintenance of prevention of relapses during the group sessions 2. Maintain the reinforcement for the achievements made, highlighting the health benefits.

### Sample size calculation

The number of subjects necessary to divide into two independent groups has been calculated. With the standard intervention, a weight reduction of 5% of weight is expected (P1) [30,31]. It was predicted that the experimental intervention would lead to 75% of the patients reducing their weight by 5%. It will be assumed an alpha risk of 0.05 (bilateral hypothesis) and a beta risk of 0.20 (a potential 80%). If the interventions will be assigned individually, in other words, per patient, the number of patients in each group would be 328 (756 in total). If we assume a percentage loss of 20% and apply a correction according to the formula Na = N [1/1-R)] where N is the theoretical number of subjects, Na is the corrected number of subjects and R is the expected proportion of loss, a total of 946 patients would be necessary. Given that the assignment of the interventions will be done by BHA, we had to increase the sample size because of the design effect [28]; if 24 BHA (clusters) were to participate, 12 per type of information, it would be K = [m(1-CCI)]/[Z-(CCI × m)] where K = number of subjects per cluster, m = 473 patients per intervention, Z = number of clusters per type of intervention = 12 and ICC = intra-class correlation coefficient. We assumed that the basic ICC for the percentage of obese patients who would reduce their weight by 5% was 0.005. The number of patients in each BHA (Cluster) would be 50. 50 subjects × 12 BHA = 600 patients per arm or type of intervention. 600 subjects × 2 interventions = a total of 1,200 patients.

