The training of the nursing staff has consisted in a basic training strategy, initially aimed at nurses and focusing on group motivation for life-style changes in overweight and obese patients, because lack of motivation is a common cause of therapeutic failure. The training has consisted of a number of workshops where role play techniques have taken place to help assimilate the concepts taught. This workshop has been delivered at the BHA of the intervention group and written material delivered regarding the content. Secondly, a written guide has been created to standardise the information the nurses provide during the overweight and obesity check-up visits. The guide includes information about the disease, healthy habits and diet.

Randomization into the study began in first trimester 2008, with a recruitment goal of 1,200 participants. The intervention and main trial recruitment will take place over 30 months with the patients in the intervention and control groups.

Finally, four months before the end of the project the final laboratory tests will be performed and the data collected for statistical analysis and reporting.

The first patient was entered on September 2008. The final visit for the last randomized participant is planned for the last trimester 2010, with final study reports expected in the first trimester of 2013.

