### Selection of the study subjects

The IMOPAP inclusion and exclusion criteria are presented in Table 2. These criteria have been established to identify a trial population with overweight and obesity, and with sufficient statistical power with the proposed sample size. They will be included sequentially, from the beginning of the study. To avoid possible bias in the selection of patients, and not overburden the nursing staff, patient recruitment and follow up will be rolled out in stages during the first six months of the study to the first two patients who meet the study inclusion requirements and who present none of the exclusion criteria. This will carry out superior quality control, using smaller sample size than would be possible if we randomised the patients. The institutional review Ethics Committee of Jordi Gol i Gurina Foundation in Barcelona approved the conduct of the study. In addition, the study has been done in compliance with the Helsinki Declaration. Each IMOAP participant has provided written informed consent using procedures reviewed and approved by the EECC review board.

**Table 2 T2:** Inclusion and exclusion criteria

*Inclusion criteria*
1. Overweight (BMI>25) and obese (BMI>30) patients of both genders, registered in the medical history (MH) or recently diagnosed.
2. Aged between 30 and 70 years
3. Agreement to participate in the study

*Exclusion criteria*
1. Patients with severe clinical pathology (bedridden, dementia, advanced neoplasia, etc.)
2. Patients with secondary obesity (hypothyroidism, Cushing's disease, etc)
3. Patients with severe sensorial disorders capable of interfering with the motivational intervention (severe, uncorrected deafness, severe visual deficit, etc).
4. Patients with serious psychiatric disorders

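### The sample-size paragraph gives 328 per group but 756 in total, and P1 is not a proportion of patients, so the 1,200 target and its 80% power cannot be derived from the stated inputs

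*Protocol article*

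**What the plan says.** All of the calculation is in the protocol article, under Sample size calculation.

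- Control input: "With the standard intervention, a weight reduction of 5% of weight is expected (P1"), supported by two references.
- Intervention input: "the experimental intervention would lead to 75% of the patients reducing their weight by 5"%.
- Error rates: "an alpha risk of 0.05 (bilateral hypothesis") and "a beta risk of 0.20 (a potential 80"%).
- Result under individual assignment: "the number of patients in each group would be 328 (756 in total").
- Loss of 20%, applied by dividing by 1 − R: "a total of 946 patients would be necessary".
- Cluster step: K = m(1 − ICC)/(Z − ICC × m), with m = 473 per arm, Z = 12 BHA per arm and ICC = 0.005. It gives 50 per BHA, 600 per arm and 1,200 in total.

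Study overview repeats the target: "with a recruitment goal of 1,200 participants". Outcomes defines the primary measure as a percentage of patients who lose 5% and keep it off. Statistical analysis states the null hypothesis as equal proportions of patients reaching a 5% loss.

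**The concern.** There are two separate faults.

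First, the per-group figure and the total contradict each other by 100 patients, and every later step uses the total. The recruitment target therefore rests on a number that disagrees with the one printed beside it.

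Second, a comparison of two proportions needs the proportion of control patients expected to lose 5%. The paragraph labels an input P1 but fills it with the size of a weight change. The planned difference between arms is therefore stated nowhere, and a power of 80% has no meaning until it is. Anyone who later reads a null result, or checks whether the trial was the right size, cannot tell what difference it was built to detect.

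**Working it through.** **Inputs.** From Sample size calculation: P2 = 0.75, two-sided alpha 0.05 (z = 1.960), power 80% (z = 0.842), loss 20%, 12 clusters per arm, ICC 0.005. P1 as a proportion of patients is not given, so every P1 below is an assumption.

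**1. The plan's own chain from 756.**
- 756/0.8 = 945. The plan has 946, which is 2 × 473.
- K = 473 × 0.995/(12 − 0.005 × 473) = 470.6/9.635 = 48.8. The plan has 50.
- At 49 per BHA: 49 × 24 = 1,176. At 50 per BHA: 50 × 24 = 1,200.

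From 756 onward the chain is coherent within rounding.

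**2. The first step.** 2 × 328 = 656, not 756. Conversely, 756/2 = 378.

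**3. P1 taken literally.** The pooled two-proportion formula, with p̄ the mean of P1 and P2, is

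n = [1.960 √(2p̄(1 − p̄)) + 0.842 √(P1(1 − P1) + P2(1 − P2))]² / (P1 − P2)².

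With 0.05 versus 0.75: (1.358 + 0.408)²/0.49 = 6.4, so 7 per group (9 with continuity correction). That is neither 328 nor 378.

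**4. Back-solving P1 with P2 = 0.75.**
- P1 = 0.65: (1.270 + 0.542)²/0.01 = 328.5 pooled. The arcsine formula gives 327.6. Rounded up, the unpooled formula gives 326 and the continuity-corrected one 349.
- 378 per group corresponds to P1 of about 0.657 (about 0.654 with continuity correction).

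**5. Reading (a): 328 is right.** 656/0.8 = 820; m = 410; K = 410 × 0.995/(12 − 2.05) = 407.95/9.95 = 41.0; 41 × 12 = 492 per arm; 984 in total. That is 216 (18%) below 1,200.

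**6. Reading (b): 378 is right.** The chain in step 1 applies: 1,176, or 1,200 at the stated 50 per BHA.

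**7. Power of 1,200 as planned.** After 20% loss, 40 patients per BHA remain. Design effect = 1 + 39 × 0.005 = 1.195. Effective n per arm = 480/1.195 = 401.7.

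| Assumed P1 | Power against 75% (normal approximation) |
|---|---|
| 0.60 | 99.6% |
| 0.65 | 87% |
| 0.657 | 82% |
| 0.66 | 80% |
| 0.67 | 71% |
| 0.70 | 35% |

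With only 24 clusters, a t reference on 22 df (critical value 2.074) is more cautious. At P1 = 0.65 the standardised difference is 0.10/√((0.2275 + 0.1875)/401.7) = 3.11, and power is about 84%. At P1 = 0.657 it is 0.093/√((0.2254 + 0.1875)/401.7) = 2.90, and power is about 79%.

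**The case against.** The strongest reply is that the fault may be one misprinted digit. Everything after 756 hangs together, so if 328 should read 378, the 1,200 target stands. The documents do not exclude this. A P1 of 65.7% is not a round number, but the plan attributes P1 to published sources, and a value taken from the literature need not be round.

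On the other side, a round 65% versus 75% lands on the printed 328 to within rounding, which makes it tempting to say that the trial was planned on a 65% control rate and a 10-point difference. The documents do not support that as a fact. Neither figure appears in them, both are back-solved from one of two conflicting numbers, and the match depends on the formula: the pooled result of 328.5 would normally be rounded up to 329. For the same reason 984 is the result of one scenario and not the correct target.

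A reader might also infer that the trial is underpowered. That is not shown. Under reading (a) 1,200 is more than the formulas require, and under reading (b) it is about what they require.

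What the reply does not remove is the mis-stated P1. Correcting 328 to 378 would make the two counts agree, but would still leave the reader without the control proportion or the planned difference.

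A side point is the sentence in Selection of the study subjects that speaks of "using smaller sample size than would be possible if we randomised the patients". It sits badly with the increase for the design effect under Sample size calculation. The sentence is garbled, follows text on staged recruitment and does not enter the calculation, so it needs clarifying and carries no weight here.

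**Conclusion.** The paragraph is wrong as written on two counts: 328 per group and 756 in total cannot both be right, and P1 is not the quantity the calculation needs. Neither the 1,200 target nor its 80% power follows from the stated inputs.

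The size of the error depends on which figure was intended. If 328, the formulas call for 984, and 1,200 gives about 84–87% power. If 378, the target stands within rounding, with about 82% power by normal approximation. Both results assume the back-solved P1, ICC 0.005, 20% loss and equal cluster sizes.

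The missing P1 matters more than the slip of 100. A shift from 0.65 to 0.67 takes power at 1,200 from 87% to 71%. The finding is that the stated power cannot be verified; it does not establish that the trial is too small or too large.

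**What to change.** 1. State P1 as the percentage of control patients expected to lose 5%, taken from the original calculation and with its source, and state the resulting difference from 75%.
2. Correct whichever of 328 or 756 is wrong, and name the sample-size formula used.
3. Re-run the loss and cluster steps with the plan's own formulas and print each result.
4. If 1,200 is kept, state the power it gives for that P1 at ICC 0.005 and 20% loss.
5. Reword the sentence on smaller sample size in Selection of the study subjects so that it agrees with the increase for the design effect under Sample size calculation.

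The cost is a rewritten paragraph and one clarified sentence. No change in enrolment is requested.

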### Statistical analysis

A descriptive statistical analysis will be made according to the variables. For the quantitative variables, using the mean and standard deviation, for the qualitative ones, proportions will be used. The data analysis will include an evaluation of the initial comparability of the patients in the two types of intervention using bivariate techniques: The Chi-Square for the proportions and, in the case of the mean, the Student's t-distribution or its non-parametric equivalent when necessary, by point estimation with a confidence interval of 95%.

The hypothesis to compare will be the null hypothesis, defined as equal efficacy of the usual and experimental interventions (both interventions achieved a weight loss of 5% in the same proportion of patients). The possible difference in efficacy between the interventions will be carried out through an analysis based on the individual values of the patients using multilevel statistical techniques [32].

## Discussion

Overweight and obesity, serious and growing health problems, are not receiving the attention they deserve from primary care practitioners. An additional problem related to weight loss, if achieved, is its maintenance.

The study IMOAP analyses the management of overweight and obesity, in a group motivational intervention, managed by a nurse trained by an expert psychologist, in addition to usual practice, to see if this intervention is more efficient than the latter alone in the treatment of overweight and obesity in relation to percentage weight loss and maintenance. Also, if so, if it would it be possible to reduce the prevalence of classic and emerging cardiovascular risk factors that are related to overweight and obesity, and, in consequence, cardiovascular conditions.

The results of IMOAP trial should provide substantial direction regarding weight loss management at a primary care, and it could be introduced as a basic treatment tool for overweight and obese patients.
